**Questionnaires**

Patient-related secondary outcome measures, potentially confounding variables and the patients’ evaluation of the telephone-intervention are assessed via self-administered paper-pencil questionnaires incorporating already validated instruments as well as asplenia-specific scales developed for the purpose of this study, which are described below.

1. ***HAPA-related outcomes*.** To gather key HAPA variables addressed in the intervention, perceived disease risk relevant to asplenia, patients’ behavioral intention to implementation, perceived self-efficacy for implementation, action and coping planning, positive and negative outcome expectations and received social support are assessed. Items were developed on the basis of the general assessment rules for HAPA constructs provided by Schwarzer et al. (20) and slightly adapted to infection prevention behavior in asplenia. Responses are rated on a six-point scale ranging from *fully correct* (1) to *not correct at all* (6) (except the scale *risk perception*)*.*

Six items measuring *behavioral intention* to obtain prevention refer, for instance, to “undertake preventive measures recommended after splenectomy” and “obtain vaccinations”. *Perceived self-efficacy* is assessed by ten items asking participants to rate their level of confidence in their ability to implement and cope with preventive measures, such as “I can correctly interpret symptoms of a severe infection” or “I will renew my emergency antibiotics after the expiration date”. *Prevention behavior* *planning* is assessed with six items, four items measuring action planning as the items address the where and how of the precautions (e.g. “what kind of vaccinations I will get done”) and two items measuring coping planning asking for situations that could interfere with their plans (e.g. “what I can do if I forget my emergency antibiotics”). *Positive and negative outcome expectancies* after implementing the preventive measures are assessed with three items asking for pros, e.g. “I’m better protected from the flu” and three items asking for cons, e.g. “I could suffer from side effects of vaccinations”. *Received social support* regarding prevention implementation is measured with the stem “People around me (e.g. family, friends)…” followed by five items, for example “have encouraged me to take preventive measures recommended after splenectomy”. For *risk perception*, the item stem “If I compare myself with other people (of my age and sex), then my risk, sometime in future…” is followed by the items “to fall ill with blood poisoning”, “to fall ill with meningitis” and “to get pneumonia”, which are rated by participants on a scale from *significantly increased* (1) to *considerably lower* (5).

1. ***Self-management*.** General self-management is assessed with the two subscales *Self-Monitoring and Insight* and *Skill and Technique Acquisition* from the German version of the Health Education Impact Questionnaire (heiQ) (26, 27), a widespread tool developed to assess proximal outcomes of patient self-management programs, covering eight independent dimensions. The scale *Self-Monitoring and Insight* (six items) captures individuals’ ability to monitor their condition that leads to insight and appropriate actions to self-manage as well as individuals’ acknowledgment of realistic disease-related limitations. The scale *Skill and Technique Acquisition* (four items) covers the subjective appraisal of knowledge-based skills and techniques that help manage disease-related symptoms and health problems. Items are scored on a 4-point response scale (1 = *strongly disagree* to 4 = *strongly agree*) and averaged for the two scales, with higher values indicate a higher subjective judgement of self-monitoring and skills respectively.
2. ***Asplenia-specific self-management and asplenia-specific health literacy.*** To capture disease-specific self-management components, five items related to asplenia were developed on the basis of the heiQ-scales *Self-Monitoring and Insight* (three items) as well as *Skill and Technique Acquisition* (two items), described above. One item each derived from the heiQ-scales *Health-Service Navigation* and *Social Integration and Support* were used to develop two further items as these aspects are additionally relevant for asplenia-specific self-management.
   A total of six items capturing asplenia-specific health literacy were derived from the Health Literacy Questionnaire (HLQ) (28). The HLQ covers nine health literacy domains that reflect an individual’s competencies and experiences when attempting to understand, access and use health-information or when trying to engage with healthcare practitioners or services, of which five were used as basis for the development of the disease-specific health-literacy items. The response format for all self-developed items is a 6-point scale ranging from *fully correct* (1) to *not correct at all* (6).
3. ***Patient involvement.*** Patient involvement is measured with the German version of the Perceived Involvement in Care Scales (PICS) (29, 30) a 14-item generic instrument that is designed to assess patients’ perceptions of participation in treatment decision making as well as physicians’ efforts to facilitate patient involvement. It covers three categories of patient-physician communication: *Doctor Facilitation of Patient Involvement, Level of Information Exchange* and *Patient Participation in Decision Making*. The response scale is a 4-point Likert scale ranging from 1 (*strongly disagree*) to 4 (*strongly agree*), where higher scores indicate higher perceived patient activity and endorsement.
4. ***Health-related quality of life.*** The 12-item Short-Form-Health-Survey (SF-12, short version of SF-36) is administered to assess self-reported health-related quality of life referring to the past four weeks (31). The SF-12 is a generic instrument that yields a subjective mental and physical health status summary score derived from four health components respectively: Physical health comprises *general health, physical functioning, role limitations due to physical health problems* and *bodily pain*; subjective mental health comprises *vitality (energy/fatigue), social functioning, role limitations due to emotional problems* and *mental health*. High scale values indicate better health.
5. ***Subjective and objective disease knowledge***. Subjective disease knowledge held by patients is assessed using two items asking them to rate their level of knowledge about the consequences of splenectomy and potential preventive measures on a 5-point scale (1 = *very great knowledge* to 5 = *non-existent knowledge*). Four additional questions are administered to ascertain the objective degree of knowledge about asplenism. The items refer to the functions of the spleen, consequences of splenectomy, recommended precautions and patients theoretically behavior in case of sudden septic symptoms (of which the latter is derived from Gundling et al. (31).
6. ***Compliance and influenza prevention behaviors.*** Patients’ compliance with general health-preserving measures is estimated using four items of the German version of the Questionnaire of Multiple Health Behavior (MHB-39) (32) that load highest onto the domain *Compliance* (i.e. having regular check-ups and prophylactic vaccinations made, complying with physicians and consulting a doctor when indicated). The MHB-39 assesses habitual health-related behaviors on a 5-point Likert scale (1 = *never* and 5 = *always*). In our questionnaire, the MHB-39 compliance-items are supplemented by three questions asking for patients influenza prevention behaviors (i.e., washing hands after return to home and before touching food, avoid touching eyes or mouth in public, avoid hand shaking during flu season) taken from Zhang et al. (17) and translated into German.
7. ***Depression and anxiety.*** Indicators of depression and anxiety in patient participants are measured using the German version of the Patient Health Questionnaire for Depression and Anxiety (PHQ-4) (33), a validated four-item ultra-brief screening instrument that consists of a 2-item *depression scale* (Patient-Health-Questionnaire, PHQ-2) (33, 34) asking for DSM-IV diagnostic core criteria symptoms (i.e. loss of interest, depressed mood) and a 2-item *anxiety-scale* (Generalized Anxiety Disorder Scale, GAD-2) (34) representing core symptoms of a generalized anxiety disorder (feeling nervous and anxious, difficulty to stop or control worrying). The stem question for all items is: “Over the last two weeks, how often have you been bothered by any of the following problems?”. Answers a given on a 4-point Likert-type scale ranging from *not at all* (0) to *nearly every day* (3). Scale scores ≥ 3 indicate the presence of a depression or an anxiety disorder, respectively.
8. ***Evaluation of the telephone-intervention*.** Patients are asked to judge patient-centered criteria of the telephone-intervention using six items relating to the content (i.e. topic selection, comprehensibility, and usefulness), materials and interaction (atmosphere, opportunity to make own comments or pose questions). Items are rated on a school grading scale ranging from (1) *very good* to (6) *very poor*. Two further open questions inquire positive feedback and suggestions for improvement. Items were taken from Meng et al. (35) and slightly adapted to our intervention.

**Procedure**

The chosen outcomes for patients are measured prior to the intervention (baseline measurement, t0), directly after the intervention (t1) and after a 6-month follow-up period (t2).

At t0, patients in the intervention group are sent paper-pencil pseudonymized questionnaires on baseline proximal and distal secondary outcomes and socio-demographic information. Upon receipt of the filled questionnaires, telephone appointments are arranged with patients for a study physician interview by study nurses. During telephone calls, a vaccination history, use and availability of stand-by antibiotics and the medical alert card are taken to gather baseline data on the primary outcome, the PrePSS-score, along with some other medical information relating to the patients’ asplenia (e.g. indication for splenectomy, splenectomy date and previous episodes of infection or PSS requiring hospitalization)

After t0-data collection, the patient-directed telephone-intervention is implemented. The intervention of the corresponding physician is conducted at about the same time; however, the order is determined by the arrangement of the telephone appointments and not standardized. Secondary physician outcomes are gathered after the physician-directed intervention. Historical control group patients and their physicians go through the same procedure and patients receive t0-questionnaires identical to intervention group patients, but only intervention participants continue measurement after the telephone intervention.

Following each patient telephone call, intervention patients complete post-intervention questionnaires on the proximal secondary outcomes similar to baseline items and evaluate the telephone-intervention (t1).

To test for six-month sustainability of the effects of the intervention they receive follow-up questionnaires on distal secondary outcomes identical to baseline measurement (t2). After return of the follow-up questionnaires, intervention patients are contacted by study physicians via telephone again to inquire the same set of data on the primary outcome and (changes in) medical data, such as the incidence of infections and PSS, gathered at t0.

To ensure a valid data basis, patients’ self-report data on the primary outcome variable and on the medical information are confirmed with the corresponding physician both at t0 and (in the intervention group) at t2. In case physicians are interviewed prior to their patients, patients are made aware of any discrepancies between their information and information their physicians provided when required.

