**Methods**

**Aims and hypotheses**

The purpose of this study is to develop, manualize and evaluate a novel intervention that educates both patients and their physicians on appropriate preventive measures that should be undertaken to prevent infections after splenectomy. Besides information provision, the intervention is intended to motivate patients to implement the preventive measures and to convey action-related skills such as planning and managing barriers. It will be evaluated whether this targeted intervention (intervention group) is superior to usual care (historical control group) in terms of primary and secondary study outcomes. More precisely, we have put forward the following hypotheses as to the outcome of the intervention: (a) Adherence to infection-risk reducing preventive measures will significantly be increased (primary outcome). As a result, (b) the incidence of severe infections associated with asplenia (particular PSS) and (c) related health-care costs covered by health insurances will be reduced (distal secondary outcomes). (d) Risk perception, intention to implementation, perceived self-efficacy, action and coping-planning, positive and negative outcome expectations and received social support (HAPA-related variables) expected to account for the effect of the intervention will significantly be enhanced (proximal secondary outcomes). Furthermore, (e) disease knowledge, patients’ general and asplenia-specific self-management, asplenia-specific health literacy, patient involvement as well as health-related quality of life will significantly be enhanced (distal secondary outcomes).

Beside this quantitative outcome-evaluation, intervention patients’ and intervention patients’ physicians’ acceptance and evaluation of the intervention will be inquired in telephone interviews in a process-evaluating part of the study.

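### No outcome is measured at both t1 and t2, so t2 shows a six-month effect rather than a sustained one, and received social support is measured too early to be tested

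*Protocol*

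**What the plan says.** The Procedure section opens with a general statement, "The chosen outcomes for patients are measured prior to the intervention (baseline measurement, t0), directly after the intervention (t1", and adds a third measurement, t2, after six months. It then assigns the outcomes one by one.

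- **t0:** patients receive "questionnaires on baseline proximal and distal secondary outcomes and socio-demographic information", and the telephone interview serves "to gather baseline data on the primary outcome, the PrePSS-score". Both groups do this.
- **t1:** "intervention patients complete post-intervention questionnaires on the proximal secondary outcomes similar to baseline items", together with an evaluation of the call.
- **t2:** "To test for six-month sustainability of the effects of the intervention they receive follow-up questionnaires on distal secondary outcomes", the same ones as at t0. A further telephone interview then repeats the PrePSS-score and the medical data.

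Controls are measured at t0 only.

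Hypothesis (d) in Aims and hypotheses lists the HAPA variables, received social support among them, as "expected to account for the effect of the intervention will significantly be enhanced (proximal secondary outcomes". It names no time point. The Secondary outcomes section expects proximal outcomes to show soon after the intervention. The Questionnaires section illustrates received social support with an item about the people around the patient, who "have encouraged me to take preventive measures recommended after splenectomy".

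**The concern.** The opening sentence of Procedure reads as if every chosen outcome were taken at all three time points. The detailed assignment does not bear this out, and two stated aims are affected.

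First, sustainability in its usual sense means that an effect seen early is still there later. That needs an early and a late reading of the same variable, and no variable has both. The HAPA scales have the early reading without the late one. The PrePSS-score and the distal outcomes have the late one without the early one.

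Second, received social support is a report of what other people have already done. The session can prompt a patient to turn to family or friends (Patient-directed intervention, planning part), but the support itself can come only afterwards. A null result at t1 would say nothing about whether the intervention works through this route, and a mediation path through t1 social support would be equally uninformative.

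**Working it through.** No sample size or power figure enters this point. The check is a cross-tabulation of the Procedure section and an item count.

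**Step 1: outcome by time point**

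| Outcome | t0 | t1 | t2 |
|---|---|---|---|
| HAPA (proximal) scales | both groups | intervention group | not assigned |
| PrePSS-score | both groups | not assigned | intervention group |
| Distal secondary outcomes | both groups | not assigned | intervention group |

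- Shared by t0 and t1: the HAPA scales.
- Shared by t0 and t2: the PrePSS-score and the distal outcomes.
- Shared by t1 and t2: none.

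Each outcome therefore has a baseline and exactly one post-intervention reading.

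**Step 2: what each pairing can answer**

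- t2 against own t0 and against control t0: whether an effect is present at six months. This is available for the PrePSS-score and the distal outcomes.
- t1 against own t0 and against control t0: whether there is a short-term HAPA change.
- t1 against t2: whether a change persists. This is available for nothing.

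**Step 3: how much of hypothesis (d) is affected**

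Item counts from the Questionnaires section:

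- intention 6
- self-efficacy 10
- planning 4 + 2 = 6
- outcome expectations 3 + 3 = 6
- received social support 5
- risk perception 3

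Total: 6 + 10 + 6 + 6 + 5 + 3 = 36. Without social support: 36 − 5 = 31 items, which can be tested at t1.

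**Step 4: items to add at t2**

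Minimum: 5 (social support). Preferred: 5 + 6 (planning) + 6 (intention) = 17.

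**Step 5: does t2 suit the group comparison for social support?**

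Controls answer at more than 6 and at most 18 months after splenectomy. Intervention patients are contacted from about 6 weeks (about 1.4 months) and are at most 4 months out at allocation (Participants and recruitment). If the call follows soon after, t2 falls between about 1.4 + 6 = 7.4 and 4 + 6 = 10 months, inside the control window. At t1 the intervention group has generally had less time to receive support than the controls. This is an inference, because the delay from allocation to the call is not given.

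**The case against.** The strongest reply is that the timing is deliberate. Proximal outcomes are expected early, hypothesis (d) sets no six-month time point, and mediators at t1 before an outcome at t2 is the right order for the mediation models in Data analysis. This stands. It is the reason to keep t1 and not to move all of hypothesis (d) to t2.

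It can also be said that sustainability may simply mean an effect at six months, and that a PrePSS-score just after the call would be pointless because vaccinations and prescriptions take time. Both are fair. On that reading the aim is achievable and only the word is too strong, but persistence of HAPA changes is still unmeasured.

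On social support, only one of the five items is shown. Materials are sent before the call and the t0 questionnaire is returned before the appointment is made, so the t0 to t1 interval is longer than the 20-minute session. Some change is possible, but a reading at t1 still misses support that the call leads patients to seek later.

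The interviews of 20 patients at 5.5 months cover implementation and barriers, but they are not scale measurements. Figure 1 is not visible and may show more. The t1 wording could be stretched to later calls, but the protocol's own definition of t1 speaks against that.

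A reader might infer that intention and planning at t1 will come out positive almost automatically, because patients have just ticked goals and noted plans on worksheets. The protocol gives no figure for this and no return interval for the t1 questionnaire, so the inference is not supported.

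**Conclusion.** The point holds in a limited form. As assigned in Procedure, the t2 data support a statement about effect at six months on the PrePSS-score and distal outcomes. They do not support a statement that an early effect was maintained, and nothing is known about HAPA changes at six months. Received social support (5 of 36 items) gets no meaningful test at t1.

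A reader might go further and conclude that hypothesis (d) as a whole cannot be answered, or that nothing about six months can be tested. The documents do not support either. Risk perception, intention, self-efficacy, planning and outcome expectations (31 items) can be compared at t1 with the patients' own t0 and with control t0, and the primary and distal outcomes can be assessed at t2.

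The primary outcome, its analysis and the sample size are untouched. The conclusion assumes that the other four social-support items are, like the example, about support already received, and that t1 falls soon after the call, as the protocol defines it.

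**What to change.** Keep t1 as the time point for the other HAPA variables and for the mediation models. Add the 5 received-social-support items to the existing t2 questionnaire, and preferably planning (6) and intention (6) as well. Test received social support at t2. Report t1 to t2 change in the repeated scales as the sustainability analysis.

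The cost is 5 to 17 more items, slightly more patient burden and possibly a slightly lower t2 return. Recruitment began in early 2019, so patients already past t2 when the change is made would lack these data. Their number should be reported.

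If the items are not added, three wording changes are needed:

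- replace the sustainability aim with *effect at six months*;
- remove received social support from hypothesis (d);
- rewrite the opening sentence of Procedure so that it says which outcomes are measured at which time point.

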**Sample size considerations**

A priori calculation of the sample size of patient participants to compare the intervention group to the historical control group in the primary outcome was performed with the software ‘*Power and Precision*‘*.* Based on an assumed medium to large effect size of 0.40, a statistical power of 80% and a significance level of 5% (two-sided) the minimum required patient sample of *N* = 100 per group was calculated. Further sample size considerations take into account the actual number of splenectomized patients insured by the AOK. An explorative request showed that 360-400 patients undergo splenectomy a year, resulting in approximately 500 patients assumed to be available for recruitment in the planned inclusion period of 18 months. Based on studies with similar patients (13), we further estimated a proportion of 50% non-respondents for the intervention group and attrition rates of 40% of respondents, so we aim to recruit 500 potential intervention group patients for an expected analysis sample of *N* =178 participants. As this exceeds the statistically required number of cases despite conservative estimations, sufficient cases will be available even after considering potential deceases in the course of the study.

Given that the inclusion period (18 months) is the same for the control group (although retrospectively), sample size considerations for this group are largely the same, with the exception of an assumed proportion of 60% non-respondents and a dropout rate of 50%, resulting in expected *N* = 110 control group cases for analysis. Correspondingly, the number of physician participants included in analysis will be *N* = 178 intervention patients’ physicians and *N* = 110 control patients’ physicians maximum, considering that some patients may have the same physician.

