**Data analysis**

Demographic characteristics of the study population and effect sizes in the intervention group will be reported descriptively. The main analysis tests the hypothesis that the PrePSS-score at follow-up is higher (better adherence to infection-risk reducing preventive measures) in the intervention group than in the control group. Due to the non-randomized design a propensity score adjustment is performed to reduce potential bias that may be caused by differences on covariates in the two groups (36). We will apply general linear models with propensity score as a covariate. The same method will be used for the analysis of secondary outcomes. Assuming missing data in the questionnaires, multiple imputation will be considered for corresponding analyses. Additional analyses will be conducted with structural equation modeling technique to test a priori specified mediation models of intervention effects.

A cost-effectiveness analysis of the intervention will be conducted by analyzing the change-from-baseline scores of the primary and the secondary outcomes in relation to the costs of the intervention. To reveal the economic efficiency of the intervention, routine data will be used to determine standard treatment and follow-up costs associated with infections requiring hospitalization and with PSS in asplenic patients to contrast them to the intervention costs.

In the qualitative analyses, the audio files of the interviews will be transcribed by an external service provider and the transcripts will be analyzed using a qualitative content analysis.

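### The 6-month primary outcome call is made only after the follow-up questionnaire comes back, so non-returners in the intervention group have no stated route to a primary outcome score

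*Protocol*

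**What the plan says.** - **Source of the score.** Under Primary outcome, the study physicians derive the PrePSS-score from telephone interviews with the patient and the practitioner. No questionnaire item enters it.
- **Timing at t2.** Under Procedure, intervention patients are first sent the follow-up questionnaire, and then: "After return of the follow-up questionnaires, intervention patients are contacted by study physicians via telephone again". The call collects the primary outcome and also updates on infections and PSS.
- **Timing at t0.** The t0 call is likewise arranged once the t0 questionnaire has arrived. Controls follow the same steps and are not measured again.
- **Other sources.** At t2 the physician is contacted to confirm what the patient reported (Procedure). The insurer's routine data come as group totals (Primary outcome).
- **Primary test.** Data analysis compares the follow-up score in the intervention group with the control group, with the propensity score as a covariate.
- **Missing data.** The only sentence is "Assuming missing data in the questionnaires, multiple imputation will be considered for corresponding analyses".
- **Expected loss.** Sample size considerations states "we further estimated a proportion of 50% non-respondents for the intervention group and attrition rates of 40% of respondents", "we aim to recruit 500 potential intervention group patients", and plans "for an expected analysis sample of *N* =178 participants". For controls it assumes 60% non-response and 50% dropout.

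**The concern.** A telephone outcome has been made conditional on a postal one. A patient who could be reached by telephone, but did not send the form back, is not called under the procedure as written. Neither the physician contact nor the insurer's data is described as a substitute source for an individual score.

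The condition bears on one group only. Both groups must return a form at t0. The intervention group must return another one after the intervention and before the measurement that enters the primary test. The outcome is adherence, and sending back a study form is plausibly related to it. Retained intervention patients may then have better scores than the full group would have had. Adding patients does not cure this. The same call collects infections and PSS, so that information is lost with it.

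The collection rule is fixed in the protocol. An analysis plan can say how to treat missing scores, but it cannot recover scores that were never sought.

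**Working it through.** **1. The plan's own sample size.** Inputs from Sample size considerations: effect size 0.40, power 80%, two-sided 5%.

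n per group = 2 × (1.960 + 0.842)² / 0.40² = 98.1, so 99. The t-test version gives 99.1, so 100. The stated 100 per group reproduces.

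**2. Expected loss in the intervention group.**
- Respondents: 500 × 0.50 = 250.
- At 40% attrition, 250 × 0.40 = 100 are lost and 150 remain.
- The protocol states 178, not 150. From 250 respondents, 178 retained means 72 lost, or 72 / 250 = 28.8%.
- Both figures run from response to analysis, so they may include losses before t0. Controls are given 50% dropout although they are measured only at t0, so the protocol evidently expects loss before any follow-up. Hence 40% is an upper bound on the planned t0-to-t2 loss. The protocol does not give the t0-to-t2 loss itself.

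**3. Shift in the intervention mean.**

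Shift = t0-to-t2 loss × (completer mean − non-completer mean).

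The gap is not in the protocol. I assume 0.25 to 0.5 SD.

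| t0-to-t2 loss | Gap 0.25 SD | Gap 0.5 SD |
| --- | --- | --- |
| 20% (assumed) | 0.05 SD | 0.10 SD |
| 28.8% (if all 72 are lost after t0) | 0.07 SD | 0.14 SD |
| 40% (upper bound) | 0.10 SD | 0.20 SD |

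Against the planned 0.40, the range 0.05 to 0.20 SD is one eighth to one half of the effect.

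**4. What such a shift does to the test.** Two-sample normal test, two-sided 5%, no true effect, control selection taken as neutral and no covariate correction. The standard error in SD units is √(1/n₁ + 1/n₂): 0.121 at 178 vs 110, and 0.129 at 150 vs 100 (100 being 500 × 0.40 × 0.50).

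| Shift | Rejection, 178 vs 110 | Rejection, 150 vs 100 |
| --- | --- | --- |
| 0.05 SD | 7% | 7% |
| 0.10 SD | 13% | 12% |
| 0.20 SD | 38% | 34% |

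Power for a true effect of 0.40 is 0.91 and 0.87 respectively, so the problem is bias and not power.

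**5. Selection on the other side.** Of those approached, the plan expects to retain 0.50 × 0.60 = 30% in the intervention group and 0.40 × 0.50 = 20% of controls. If retention tracks adherence in both groups, control scores are also raised, and part of the shift cancels.

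**The case against.** Four stronger readings are tempting, and the protocol does not support them.

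- **That the plan prescribes a completer analysis.** A reader might infer this from an analysis sample stated net of attrition and an imputation sentence limited to questionnaires. The protocol does not say that patients without a t2 score are excluded, and a missing-data rule for the primary outcome may stand in a statistical analysis plan that is not at hand. The missing rule is therefore not part of this point. The collection rule is.
- **That 40% are lost at the t2 step.** The figure covers loss from response to analysis, so it is only a ceiling.
- **That the bias surely favours the intervention, or could equal the whole target effect.** The latter needs a gap of 1.0 SD at 40% loss, and the protocol supports neither. On its own figures controls are the more heavily selected group overall, 20% against 30% retained, and they too had to return a form before being scored. The intervention group's second return step, after treatment, remains particular to it, but the net direction is open.
- **That a propensity score cannot help.** The t0 questionnaire holds compliance, intention and self-efficacy items. So far as form return follows such traits, adjustment would remove part of the selection. Selection on what happens after t0 would remain.

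Two objections to remedies also stand. A physician may not know whether the antibiotic is at hand or the card is carried, and those two parameters hold 4 of the 10 points. Carrying the t0 value forward is not neutral either: intervention patients enter at most 4 months after splenectomy, controls at more than 6 and up to 18 months, so an early value allows less time for vaccination than controls had.

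**Conclusion.** The point holds as a fault in data collection. The protocol gives no route to a t2 primary outcome score for an intervention patient who does not return the follow-up form, although nothing in the score requires the form. This adds a post-intervention selection step in one group of a non-randomised comparison, and the planned covariate adjustment would correct it only in part.

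The size cannot be fixed from the protocol. With assumed gaps of 0.25 to 0.5 SD, the shift in the intervention mean is 0.05 to 0.10 SD at an assumed 20% loss and 0.10 to 0.20 SD at the 40% ceiling. These figures treat control selection as neutral. Because selection among controls at t0 may offset part, neither the net size nor the net direction is established. The change is still worth making, because the selection is avoidable and cheap to reduce.

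**What to change.** 1. **Procedure.** Make the t2 PrePSS call at 6 months to every intervention patient with a t0 score, whether or not the questionnaire has come back.
2. **Patients not reached.** Where the patient has given the release, seek the physician's t2 information on vaccinations and antibiotic prescription. Treat antibiotic availability and card carrying as missing; do not score them from the physician alone.
3. **Primary analysis.** Include all intervention patients with a t0 score, imputing missing t2 components from the t0 score and covariates.
4. **Sensitivity analysis.** Setting a missing t2 score to the t0 value may be shown only as a sensitivity analysis, labelled as conservative against the intervention because of the shorter time since splenectomy.
5. **Reporting.** Give the number lost between t0 and t2 separately from losses before t0.

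The cost is at most about 100 further short calls by the existing study physicians (250 × 0.40), or about 72 if 178 of 250 are retained (250 − 178), and fewer if part of the loss falls before t0. The effect estimate may become smaller. Deaths and withdrawals will remain missing under any scheme.
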